**Secondary outcome:**

- Mean change in the weight for height.
- Mean change in the Height for age.
- Change in level of maternal knowledge and practice of recommended infant and child feeding practice following intervention.
- Change in proportion of infants who were consuming foods from four or more food groups
- Change in proportion of infants who were consuming the recommended number of meals and snacks per day

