**IV. Maternal knowledge regarding breastfeeding and complementary feeding practices**

1. Which milk is best for the baby?

1.Breast milk 2.Formula milk 3.Animal milk 4. Don’t know

1. Up to which month exclusive breast feeding should be given?

1. Up to 6 months 2.4-6 months 3.7-8 months 4.Don’t know (998)

1. Can bottle feeding be given to baby? 1.Yes 2.No 3.Don’t know(998)
2. At what age complementary foods (solid, semisolid or soft foods) should be introduced? 1.4-6 months 2.At 6 months 3.7-8 months 4. Don’t know(998)}
3. Name three complementary foods that you think are good for a6-9 month old baby? ………………………………………………………………..(1.Know 2.Don’t Know(998))

(Note: If respondent answer any 3 food items then select option1.Eg: Khichidi, sujikheer, mashed fruits and vegetable, roti, mashed dhal, rice with dal, dhaliya with milk, basen or attacheera etc. If respondent say fruit juice, dhal water, milk then select option 2)

1. How many times a day solid/semi-solid foods should be given to 6-8 months baby? 1.= 3or more times 2. 1-2 times 3.Don’t know (998)
2. What should be the consistency of food given to baby? 1. Thick 2.Thin 3.Very thin
3. Name three snacks that can be given to a 6-8 month old baby? ……………………………………………………(1.Know 2.Don’t Know(998)) (Note: If respondent answer any 3 food items then select option1.Eg: fruits- banana, apple, papaya, mango,chiku,orangeetc, murmura, biscuits. If respondent say kurkure, chocolate, chips, fruity then select option 2)
4. What is the quantity of solid/semi-solid foods your child can consume at his/her age per feed?

| 1. 1-2 teapoonfuls | 1. 1/2 of a 250 ml cup |
| --- | --- |
| 1. 3-5 teapoonfuls | 1. 3/4^th^ of a 250 ml cup |
| 1. 2-3 tablespoonfuls | 1. Full cup |
| 1. 4-5 tablespoonfuls |  |

1. Can tea / sugar drinks/ coffee can be given to your child? 1.Yes 2. No
2. Should ghee or oil be used in complementary foods? 1.Yes 2. No 3.Don’t know (998)
3. Do you know till what age breastfeeding can be continued?
    1.Less than 1 year 2. 1 year - < 2 years 3.Upto& beyond 2 years 4. Don’t know (998)
4. Are commercial baby foods better for infants than homemade foods? 1.Yes 2.No 3.Don’t know (998)
5. Do you need to wash hands with soap and water before feeding the child? 1.yes 2. no
6. If your child is not taking food, should he/she be threatened or bribed?
    1. Yes 2. No 3. Sometimes

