**ANNEXURE -3**

**QUESTIONNAIRE FOR HEALTH WORKERS**

**Department of Community Medicine, PGIMER**

**Title: Effectiveness of a culturally appropriate nutrition educational intervention delivered through health services to improve growth and complementary feeding of 6 months to 1 year old infants in Chandigarh: a quasi experimental study.**

1. **Basic information of ANM:**
2. ID No.
3. Name - ……………………….
4. Age - ………………………………
5. Sex – 1= M, 2= F
6. Address - ……………………………………………………..
7. Phone no. ……………………………….
8. Religion………1. Hindu 2. Muslim 3. Sikh 4.Christian 5.Others
9. Education- ………… (lliterate-1, primary school certificate- 2, middle school certificate - 3, High school certificate - 4, Intermediate or post high school diploma-5, Graduate or post graduate - 6, Professional or Honours- 7)
10. Employment status - 1.Regular 2.contract.
11. Years of service as ANM: 1. 1-3years 2. 4-6 years 3. 7-9 years 4. 10 years or more
12. **Knowledge of ANMs regarding IYCF practices**
13. When will breastfeeding be initiated after birth?

1.Immediately,within 1 hour 2.>1 hour-4 hours 3.5-24 hours 4.After 24 hours.

1. Mother’s first milk (colostrum) should be given to newborn baby?

1.Yes 2.No

1. Do you know what is exclusive breast feeding? (Choose one option)

a. Breast milk only b. Breast milk and water c. Breast milk and/or ORS/Vitamin supplements/Medicines)

(1.Yes 2. No)

1. Can bottle feeding be given to the child? 1.Yes 2. No 3. Don’t know
2. At what age complementary foods (solid, semisolid or soft foods) should be introduced? ………………………………… {1.correct 2. Incorrect 3. Don’t know}
3. Name three complementary foods that you think are best for an infant 6-8 months old? 1.……………………2……………………3…………………(1.Know 2.Don’t Know)
4. How many times a day solid/semi-solid foods should be given to 6-8 month old infant? 1. Once a day 2. 2-3 times 3. 4-5 times 4.Don’t know
5. What should be the consistency of complementary foods given to the infant? 1.Thick 2.Thin 3.Very thin
6. Name three snacks that can be given to a 6-8 month old infant? 1…………..………2………….………3…………………(1.correct 2. incorrect)
7. What is the quantity of solid/semi-solid foods a 6-8month infant can consume at his/her age per feed?
8. Start with 1-2 teaspoons and increase to 1/4^th^ of a 250 ml cup
9. Start with 2-3 tablespoons and increase to 1/2 of a 250 ml cup
10. Start with 4-5 tablespoons and increase to 3/4^th^of a 250 ml cup
11. Full cup
12. Can tea / sugar drinks can be given to the infant? 1.Yes 2. No

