- the key messages to share with caregivers and your co- workers.

Key Messages:

1. A growing child needs three meals plus snacks: give a variety of foods.
2. A growing child needs increasing amounts of food.

| Age | Texture | Frequency | Amount at each meal |
| --- | --- | --- | --- |
| from 6 months | Soft porridge, well  Mashed vegetable, meat, fruit | two times per day plus  frequent breastfeeds | 2 to 3 tablespoonfuls |
| 7 to 8 months | Mashed foods | Three times per day plus frequent breastfeeds | increasing gradually to  2/3 of a 250 ml cup at  each meal |
| 9 to11 months | Finely chopped or  Mashed foods, and foods that baby canpick up | three meals plus one  snack between meals  plus breastfeeds | 3/4 of a 250 ml  cup/bowl |
| 12 to 24 months | Family foods, chopped or mashed if necessary | three meals plus two  snacks between meals  plus breastfeeds | A full 250 ml cup/bowl |

1. *Feeding During Illness and Recovery*

In this session we will look at:

- - - the importance of continuing to feed a child during illness;
  - ways of encouraging children to eat during illness and recovery; and counseling caregivers on appropriate feeding practices during illness.

Key Messages:

1. Encourage the child to drink and to eat during illness and provide extra food after illness to help them recover quickly.

***Session 2-*** Communication Skills:

***1.*** *Listening and learning skills*

In this session we will discuss:

- How to use basic counseling skills to listen and learn from caregivers about their complementary practices. For example:

- 1. Use helpful non-verbal communication
  2. Ask open questions
  3. Use responses and gestures that show interest
  4. Reflect back what the caregiver says
  5. Empathize – show that you understand how she/he feels
  6. Avoid words that sound judging

1. *Building confidence skills*

In this session we will discuss:

- How to use basic counseling skills to build confidence and give support to caregivers about their complementary feeding practices.

1. Accept what a caregiver thinks and feels
2. Recognize and praise what a caregiver and child are doing right
3. Give practical help
4. Give a little relevant information
5. Use simple language
6. Make one or two suggestions, not commands

***Session 3-*** Home visit tasks and procedures:

***1.*** *Gathering Information on Complementary Feeding Practices*

In this session we will look at:

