1. KEY MESSAGES FOR COMPLEMENTARY FEEDING
   1. Breastfeeding for two years of age or longer helps a child to develop and grow strong and healthy.
   2. Starting other foods in addition to breast milk at six months helps a child to grow well.
   3. Foods that are thick enough to stay in the spoon give more energy to the child.
   4. Animal foods are especially good for children, to help them grow strong and lively.
   5. Peas, beans, lentils, and nuts and seeds, are good for children.
   6. Dark green leaves and orange colored fruits and vegetables help the child to have healthy eyes and fewer infections.
   7. A growing child needs three meals and snacks: give a variety of foods.
   8. A growing child needs increasing amounts of food.
   9. A young child needs to learn to eat: encourage and give help…with lots of patience.
   10. Encourage the child to drink and to eat during illness and provide extra food after illness to help them recover quickly.

B.AMOUNTS OF FOODS TO OFFER

| Age | Texture | Frequency | Amount at each meal |
| --- | --- | --- | --- |
| from 6 months | Soft porridge, well  Mashed vegetable, meat, fruit | two times per day plus  frequent breastfeeds | 2 to 3 tablespoonfuls |
| 7 to 8 months | Mashed foods | Three times per day plus frequent breastfeeds | increasing gradually to  2/3 of a 250 ml cup at  each meal |
| 9 to11 months | Finely chopped or  Mashed foods, and foods that baby canpick up | three meals plus one  snack between meals  plus breastfeeds | 3/4 of a 250 ml  cup/bowl |
| 12 to 24 months | Family foods, chopped or mashed if necessary | three meals plus two  snacks between meals  plus breastfeeds | A full 250 ml cup/bowl |

C. FIVE WAYS TO KEEP SAFE FOODS

1. Keep the hands clean

Wash your hands before handling food and often during food preparation.

Wash your hands after going to the toilet, changing the baby or in contact with animals. Wash very clean all surfaces and equipment used for food preparation or serving. Protect kitchen areas and food from insects, pests and other animals.

2. Separately keep the raw foods and cooked foods

Use separate equipment and utensils for handling raw meat and foods.

Store foods in separate covered containers.

3. Cook thoroughly

Cook food thoroughly, especially meat, poultry and eggs. Bring foods like soups and stews to boiling point.

For meat and poultry, make sure juices are clear not pink.

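### The 6–8 month frequency and amount items in the knowledge questionnaires match neither each other nor the training modules, so some answers that follow the modules cannot be recorded distinctly

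*Protocol*

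**What the plan says.** **Outcome.** The Protocol lists as a secondary outcome "Change in level of maternal knowledge and practice of recommended infant and child feeding practice following intervention". Mothers answer Annexure 2 and health workers answer Annexure 3. Each form is used at baseline and endline in both areas (Baseline Assessment; Post-intervention phase).

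**Frequency at 6–8 months.** Annexure 2, section IV, asks mothers "How many times a day solid/semi-solid foods should be given to 6-8 months baby? 1.= 3or more times 2. 1-2 times", with a don't-know code as the remaining option. Annexure 3 offers workers "1. Once a day 2. 2-3 times 3. 4-5 times" or don't know.

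**Amount.** For an infant of 6–8 months, Annexure 3 gives four options with upper limits of 1/4, 1/2, 3/4 and a full 250 ml cup. The second reads "Start with 2-3 tablespoons and increase to 1/2 of a 250 ml cup". Annexure 2 asks mothers how much their own child can take per feed, once under knowledge (section IV) and once, in the same words, under current practice (section V).

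**Teaching.** Annexures 4 and 5 carry the same feeding table. From 6 months it gives "two times per day plus" breastfeeds and an amount of 2 to 3 tablespoons. At 7–8 months it gives three times a day, with the amount rising to "2/3 of a 250 ml cup at" each meal. The modules are delivered in the study area; the control area keeps routine health education.

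**The concern.** A knowledge questionnaire used to evaluate teaching should be able to record what was taught. Here the age band 6–8 months spans two rows of the module table, the two forms cut the frequency answers at different points, and one taught amount has no box on the workers' form.

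This goes beyond scoring detail that could wait for an analysis plan. Once two feeds a day shares a code with one, or a 2/3-cup answer has been forced into another option, no later key can recover it. Respondents who follow the modules should be commoner in the study area at endline, so a difference in differences would not necessarily cancel the error. At stake is some understatement of the change in maternal knowledge, and a muddied comparison of workers' knowledge.

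**Working it through.** The plan states no figure on this point, so the check sets the options side by side.

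**1. Frequency at 6–8 months.** Each numeric answer, coded on both forms:

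| Feeds per day answered | Mothers' form | Workers' form | Module row |
| --- | --- | --- | --- |
| 1 | 1–2 | once | none |
| 2 | 1–2 | 2–3 | from 6 months |
| 3 | 3 or more | 2–3 | 7–8 months |
| 4 or 5 | 3 or more | 4–5 | none |

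The mothers' form splits the two taught values and joins two with one. The workers' form keeps the two taught values together and apart from one. The same answer is classed differently on the two forms, but only the mothers' item separates a taught value from the other.

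**2. Amount, workers' form.** The module's upper amount at 7–8 months is 2/3 cup. The options end at 1/4, 1/2, 3/4 and 1 cup, so none matches. The item names a fixed infant age, so it applies in the same way at baseline and endline.

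**3. Amount, mothers' form.** The cup options are 1/2, 3/4 and full in the knowledge section, and 2/3, 3/4 and full in the practice section. The lists differ although the question is the same. The missing 2/3 option matters little in the knowledge section, because the question concerns the child's current age. Infants enrol at 4–6 months and are measured again at 6 months of intervention: 4 + 6 = 10 and 6 + 6 = 12 months. The module then gives 3/4 cup (9–11 months) or a full cup (from 12 months), and both lists contain both.

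**4. Items affected.** One maternal knowledge item (frequency) and one worker knowledge item (amount). Each form has about 15 knowledge items. If they were equally weighted, which the Protocol does not say, one item would be 1/15 = 6.7% of the score.

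**5. Direction, on assumed figures only.** Suppose true knowledge on one item rises from 30% to 80% in the study area and from 30% to 40% in the control area. The true difference in differences is (80 − 30) − (40 − 30) = 40 points. Let a share m of correct answers be miscoded.

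- In both arms at both times: 40 × (1 − m) gives 36, 32 and 28 points for m = 10%, 20% and 30%.
- Only in the study area at endline, as an extreme: 80 × (1 − m) − 30 − 10 gives 32, 24 and 16 points.

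The estimate shrinks in both cases. The second is a limiting case and not what the Protocol implies. These figures concern a single item and would be diluted in any total score.

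**The case against.** **Is the error confined to the intervention arm?** A reader might infer so, because only that arm is taught. The documents do not support it. The same forms go to both areas at both times, and a control respondent who gives the same answer gets the same code. Routine health education continues in the control area, and its content is not stated. What stands is that such answers are probably commoner in the study area at endline.

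**Are taught respondents scored wrong?** No correct answer is marked for these items; the order of the mothers' options only suggests that three or more is intended. Most taught mothers would land there anyway. The 7–8 month row fits it, a key message in Annexure 5 recommends three meals and snacks without an age limit, and the second session is held at 9–11 months. Only a mother who recalls the 6-month starting row falls into the lower band. This objection largely stands and limits the size of the problem.

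**Are two worker items affected?** A reader might count frequency as well as amount. The workers' 2–3 band holds both taught values, so it penalises nobody. On amount, a trained worker could recognise the option that begins with the module's starting quantity. It is therefore not shown that learning lowers the workers' score. The mismatch in the upper limit remains.

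**Conclusion.** The point holds as an inconsistency between Annexures 2, 3, 4 and 5. The mothers' frequency item cannot separate the module's 6-month value from one feed a day. The workers' amount item cannot record the module's upper amount for 7–8 months. The mothers' two amount questions use different lists.

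The consequence is small. It reaches about one maternal item within one secondary outcome, and one worker item; worker knowledge is assessed but is not a listed outcome. The primary outcome, change in weight for age, is untouched. Any bias would tend to understate the knowledge effect. That direction rests on two assumptions: that answers following the modules are commoner in the study area at endline, and that the unseen key does not credit them. The share of a total score cannot be stated, because the Protocol defines neither a total nor weights. The passages must be reconciled; which feeding value is right is not a matter for this review.

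**What to change.** Before baseline, reconcile the feeding tables in Annexures 4 and 5 with the response options in Annexures 2 and 3, so that all four use the same age bands and categories. Give the mothers' two amount questions one common option list. The investigators should settle the feeding values themselves; neither the module table nor the questionnaire options should be presumed correct. The cost is rewording a few items and a short repeat of the pretest.

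If baseline data are already collected, do not change the options between baseline and endline. Leave the unreconciled items out of any knowledge score, in both arms and at both times. The cost is slightly less content in that score.

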**Study population**

The study population will be mother-infant dyad with infant in age group 4-6 months at enrollment;auxiliary nurse midwives (ANM) and *anganwadi* workers (AWW) in the study and control area.

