**4. Post-intervention phase**

End line assessment of maternal knowledge of infant feeding and infant feeding practices, 24 hour dietary recall (consuming foods from 4 or more food groups, recommended number of meals and snacks per day) will be done by using the same pretested semi-structured questionnaire as was used in baseline assessment in study and control area (Annexure 2). The status of undernutrition will be assessed by anthropometry of the infant (wt/age, wt/length, length/age). Similarly, the knowledge of ANMs and *anganwadi* workers on infant feeding and status of growth monitoring will be checked by the same pretested semi-structured questionnaire (Annexure 3) in both intervention and control arm.

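### Two of the 15 maternal knowledge items in Annexure 2 have answer options that do not fit the taught feeding schedule (minor, nearly free to fix)

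*Protocol*

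**What the plan says.** The Protocol lists as a secondary outcome "Change in level of maternal knowledge and practice of recommended infant and child feeding practice following intervention". The post-intervention section says the endline assessment uses "the same pretested semi-structured questionnaire as was used in baseline assessment in study and control area".

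Annexure 2, section IV, holds 15 maternal knowledge items. Two matter here.

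- **Frequency item:** "How many times a day solid/semi-solid foods should be given to 6-8 months baby? 1.= 3or more times 2. 1-2 times", followed by a code for don't know.
- **Amount item:** "What is the quantity of solid/semi-solid foods your child can consume at his/her age per feed". Seven amounts are printed, from one or two teaspoonfuls to a full cup. There is no code for none yet and none for don't know.

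The feeding table is the same in Annexure 4 (health workers) and Annexure 5 (mothers). The row for infants from 6 months reads "two times per day plus" frequent breastfeeding. The row for 7 to 8 months reads "Three times per day plus frequent breastfeeds". Annexure 4 also says that most babies need no complementary food before six months.

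The health workers' form (Annexure 3) asks about the same age with different groupings: "How many times a day solid/semi-solid foods should be given to 6-8 month old infant? 1. Once a day 2. 2-3 times".

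The study population is the "mother-infant dyad with infant in age group 4-6 months at enrollment".

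**The concern.** A knowledge item is useful only if its answer codes can tell a mother who learned the lesson from one who did not. On frequency, one question covers an age band for which the modules teach two different numbers. Those numbers fall in opposite codes, and the lower one shares a code with an inadequate answer. On amount, the item refers to the child's own age, and at baseline many of the children will be at an age when the taught amount is nothing.

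At stake is how the maternal-knowledge outcome can be read. The form, not the analysis, fixes what is recorded. Answers pooled at collection stay pooled, whatever key is written later.

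**Working it through.** The Protocol gives no figure for this point, so the check matches answer codes to the taught schedule.

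**Frequency item (asked about 6-8 months)**

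- Taught at 6 months: two a day. This falls in code 2, with one a day.
- Taught at 7 to 8 months: three a day. This falls in code 1.

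There are three possible keys:

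1. Only code 1 is right: a mother who recalls the six-month row is marked wrong.
2. Only code 2 is right: once a day is marked right, and the 7-8 month answer is marked wrong.
3. Both are right: once a day is still marked right.

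No key separates two from one. The workers' form groups two with three, so for that form a key that accepts both taught numbers and rejects one a day is possible.

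**Amount item (asked about the child's current age)**

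- Under six months: the teaching is that most infants need none. 0 of 7 options say so.
- From 6 months: 2 to 3 tablespoonfuls is taught, and it is listed.
- 7 to 8 months: a gradual rise to 2/3 of a 250 ml cup is taught. That amount is not listed; the nearest options are 1/2 and 3/4. The practice item in section V does list it.
- 9 to 11 months: 3/4 cup is taught, and it is listed.
- From 12 months: a full cup is taught, and it is listed.

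Baseline is at 4 to 6 months. Six months later the infants are about 4 + 6 = 10 to 6 + 6 = 12 months old. The gap therefore arises at baseline. The missing 2/3 cup concerns an age that falls at neither visit and is a tidying matter. The skip for infants under six months sits in section V (current practices) and does not reach section IV.

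**Size, assuming equal weight per item (the Protocol does not state this)**

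- One item: 1/15 = 6.7% of the score. Two items: 2/15 = 13.3%.
- Frequency item, if only code 1 is keyed right. Let d be the intervention-minus-control difference in the share of mothers answering two. The item difference moves by d and the score difference by d/15. For d of 0, 5 and 10 percentage points, that is 0, 5/15 = 0.33 and 10/15 = 0.67 points. The Protocol gives neither a value nor a sign for d.
- Amount item. Let u be the share of infants under six months at baseline, and k the share of their mothers who know that no food is due and so lose the mark for want of an option. The baseline score is then too low by u × k/15, which ranges from 0 to 6.7 points, and within-arm change is too high by the same amount. The between-arm distortion is (u₁k₁ − u₀k₀)/15. It is zero if both arms have the same u and k. If u differs by 10 percentage points and k = 1 in both arms, it is 10/15 = 0.67 points.

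**The case against.** A reader might infer that the frequency item biases the comparison toward no effect, because the intervention arm is marked down for what it was taught. The documents do not support that. Answering three or more fits the 7-8 month row, and it fits the key message in both modules that a growing child needs three meals plus snacks. Two appears only in the starting row. The second education session comes at 9 to 11 months, when the taught number is three plus a snack. Nothing shows that intervention mothers would answer two more often than controls; the reverse is as plausible.

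On the amount item, both arms share the 4-6 month entry criterion, so most of the artefact should cancel between arms. Infants already six months old have a valid option, as do infants at endline. Two other items in section IV capture knowledge of when solids should begin: the duration of exclusive breastfeeding and the age of introduction.

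The questionnaire is described as pretested. The workers' form is a separate instrument whose results are not a listed outcome, so its different grouping is no contradiction in the analysis. A scoring key may properly sit in a statistical analysis plan that is not shown, so its absence is not a fault.

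All of this limits the harm. It does not remove the two facts on the form: two is recorded together with one, and the amount item has no answer for an infant not yet due solids. Pretesting might have caught them, but the printed options still carry them.

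**Conclusion.** The point holds as a small flaw in the instrument for one secondary outcome. The frequency conflict is confined to six months of age, and the direction and size of any between-arm bias are unknown. On the amount item, within-arm change mixes knowledge with the infant's age, by up to 6.7 points of an equally weighted score. The between-arm difference is little affected if baseline ages are alike. That is likely under a common entry criterion but not guaranteed with two purposively chosen areas.

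It would go too far to say that the section cannot measure knowledge of the schedule: 13 of the 15 items are not in question, and these two work for the 7-8 month frequency and for the endline amounts. The meals-and-snacks outcome does not rest on the pooled codes, because section V records the feeds actually given as a count from 0 to 5. The primary weight outcome, the sample size and the error rates are unaffected. This is a minor improvement, worth making because it costs almost nothing before baseline and the pooled answers cannot be recovered afterwards.

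**What to change.** **Frequency item:** record the number of feeds the mother states, or ask separately for 6 months and for 7 to 8 months, as the module table does.

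**Amount item:** add codes for none yet (under six months) and for don't know, and list 2/3 cup. Alternatively, ask at both visits about one fixed age, such as 9 to 11 months, so that the right answer does not change as the child grows.

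**Cost:** rewording two items on one form before baseline, with no added visits, staff or data. If forms are already in use, the pooled answers cannot be split; showing any knowledge score with and without the two items would then be a reasonable check.
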